# Self Help Plus: study protocol for a cluster-randomised controlled trial of guided self-help with South Sudanese refugee women in Uganda

**DOI:** 10.1017/gmh.2018.17

**Published:** 2018-08-13

**Keywords:** Armed conflict, humanitarian emergencies, interventions, mental health, psychological intervention, trial protocol

## Abstract

**Background.:**

Exposure to armed conflict and forced displacement constitute significant risks for mental health. Existing evidence-based psychological interventions have limitations for scaling-up in low-resource humanitarian settings. The WHO has developed a guided self-help intervention, Self Help Plus (SH+), which is brief, implemented by non-specialists, and designed to be delivered to people with and without specific mental disorders. This paper outlines the study protocol for an evaluation of the SH+ intervention in northern Uganda, with South Sudanese refugee women.

**Methods.:**

A two-arm, single-blind cluster-randomised controlled trial will be conducted in 14 villages in Rhino Camp refugee settlement, with at least 588 women experiencing psychological distress. Villages will be randomly assigned to receive either SH+ with enhanced usual care (EUC), or EUC alone. SH+ is a five-session guided self-help intervention delivered in workshops with audio-recorded materials and accompanying pictorial guide. The primary outcome is reduction in overall psychological distress over time, with 3 months post-treatment as the primary end-point. Secondary outcomes are self-defined psychosocial concerns, depression and post-traumatic stress disorder symptoms, hazardous alcohol use, feelings of anger, interethnic relations, psychological flexibility, functional impairment and subjective wellbeing. Psychological flexibility is a hypothesised mediator, and past trauma history and intervention attendance will be explored as potential moderators.

**Discussion.:**

This trial will provide important information on the effectiveness of a scalable, guided self-help intervention for improving psychological health and wellbeing among people affected by adversity.

**Trial Registration::**

ISRCTN50148022; registered 13/03/2017.

The world is experiencing unprecedented rates of forced displacement due to armed conflicts and other humanitarian crises, with a current estimate of 65.6 million displaced people globally (United Nations High Commissioner for Refugees, 2017). Exposure to armed conflict, displacement and other adversities may have detrimental effects on the mental health of affected populations, and lead to increased risk for symptoms of depression (>17%) and post-traumatic stress disorder (PTSD; >15%) (Steel *et al*. 2009). High rates of psychological distress are associated with significant functional impairment, impacts on physical health and reduced ability to care for and adequately protect oneself and dependents. This has significant subsequent effects on communities and health-care resource utilisation (Norris *et al*. 2002; Prince *et al*. 2007). Ongoing stressors such as poverty and gender-based violence (GBV) commonly experienced in humanitarian settings likely also interact with trauma histories as determinants of mental health in displaced populations (Miller & Rasmussen, 2010; Miller & Jordans, 2016). As such, addressing mental health and psychosocial wellbeing is increasingly seen as a priority in humanitarian settings (Inter-Agency Standing Committee, 2007; United Nations High Commissioner for Refugees, 2013; Ventevogel *et al*. 2015).

Evidence exists for the efficacy of psychological treatments such as cognitive–behavioural therapy in treating psychological distress and disorders (Dua *et al*. 2011; Tol *et al*. 2013), and there is an increasing interest in the research on the applicability, acceptability, effectiveness, implementation and dissemination of these interventions across cultures and contexts (Murray *et al*. 2014; Kane *et al*. 2016). Yet to date, the vast majority of research on mental health interventions for populations exposed to adversity has been conducted in high-income settings (Saxena *et al*. 2007). Significant gaps exist in access to mental health services in low- and middle-income countries (LMICs) and most people in low-resource settings with mental health problems, including refugees, currently do not receive evidence-based care (Saxena *et al*. 2007; Kane *et al*. 2014). In addition, most armed conflicts occur in LMICs (Kim & Conceição, 2010), and these countries also host around 90% of the world's refugees (OECD, 2016). Thus, the damaging effects of armed conflict and displacement frequently lead to increased risk factors and greater mental health needs in the very contexts where health and support systems are greatly challenged to cope with this burden.

For psychological interventions to have promising potential for large-scale implementation in low-resource settings, they must be brief, inexpensive and relatively easy to deliver. Given the dearth of mental health specialists in most regions, particularly in humanitarian crises, scalability can be improved by: (i) further innovating on task-shifting/task-sharing approaches whereby non-specialists are trained and supervised to deliver programmes (Blanchet *et al*. 2013); (ii) enhancing reach *via* approaches targeting a broader array of mental health difficulties simultaneously (Betancourt *et al*. 2014; Murray, 2014; White & Ebert, 2014); and (iii) designing interventions to be more easily adaptable to culture and context (Castro *et al*. 2004; Bernal & Sáez-Santiago, 2006; Castro *et al*. 2010).

To meet these demands, the WHO has published guidelines and evidence-based interventions for use in non-specialised health settings (World Health Organisation, 2015*b*; World Health Organisation, 2016).

## Self Help Plus

In line with the recommendations for stress management interventions (Tol *et al*. 2013) and the need for innovative approaches to address the issues of access and scale, the WHO developed the Self Help Plus (SH+) intervention (Epping-Jordan *et al*. 2016). The programme was developed with experts in psychological intervention and global mental health, with peer review from 43 external experts. SH+ is brief (five sessions) and does not require diagnostic assessment since it aims to target a broad range of psychological difficulties (e.g. depressive and/or anxious mood, stress reactions and client-defined psychosocial problems) that cause distress but do not necessarily meet the diagnostic criteria for a mental disorder. Innovative features include a guided self-help format, comprising an illustrated book and audio materials (which provide the core course content) delivered in a larger group course format, with a guide to assist briefly trained lay facilitators to conduct the course. These materials aim to ensure that key intervention exercises are delivered with fidelity, without the financial and human resource burden of extensive training and supervision. Thus, SH+ may be easier to disseminate and more readily scalable in areas where there is limited access to mental health services.

SH+ is based on Acceptance and Commitment Therapy (ACT), a third-wave cognitive–behavioural approach that incorporates acceptance and mindfulness and encourages meaningful living despite adversity. Specifically, ACT aims to promote psychological flexibility, which is associated with (i) a reduction in attempts to alter or control unwanted internal experiences such as thoughts and emotions (based on the notion that suppressing unwanted thoughts and emotions paradoxically increases them) and (ii) an increased ability to respond adaptively to situations for the purpose of valued living (Hayes *et al*. 2006). Arguments for using ACT in efforts to increase access to mental health support in culturally varied low-resource settings have been highlighted recently (White *et al*. 2017). Several meta-analyses suggest that ACT-based interventions may be effective in various formats, and for numerous psychosocial problems (Hayes *et al*. 2006; A-Tjak *et al*. 2015), including in low-resource and culturally varied settings (Lundgren *et al*. 2006; Stewart *et al*. 2016).

Current progress in psychological research and practice has targeted increased access through innovative delivery models such as psychoeducational courses (Cuijpers *et al*. 2009), e-mental health (Andrews *et al*. 2010) and bibliotherapy (Cuijpers *et al*. 2010). Recent meta-analyses suggest that (i) guided self-help formats may be just as effective as face-to-face interventions for depression (World Health Organisation, 2015*a*); and (ii) self-help mindfulness-based interventions are potentially efficacious in reducing depression and anxiety (Cavanagh *et al*. 2014). Several ACT interventions have been tested in self-help format (Fledderus *et al*. 2012; Jeffcoat & Hayes, 2012; Trompetter *et al*. 2015).

## Setting

This study is part of a larger programme of research being conducted in Rhino Camp refugee settlement, located in northern Uganda. Despite its name, Rhino Camp is not a camp but a set of villages where South Sudanese refugees are able to self-settle on appointed plots of land and utilise existing government health and education services. Most recent figures indicate that approximately 116250 South Sudanese refugees reside in Rhino Camp ([name], Health Information System Officer, Public Health Section, UNHCR, Geneva).

High rates of mental health problems have been documented in displaced South Sudanese populations, with co-occurring PTSD, depression and anxiety symptoms the most commonly reported (Harsha & Kulkarni, 2014). Local idioms of distress among South Sudanese have also been documented (Ventevogel *et al*. 2013). A recent desk review and needs assessment conducted in Rhino Camp during early phases of this study found high levels of psychological distress among displaced South Sudanese populations. Experiences of GBV, including sexual violence, and early marriage were common. Limited mental health and psychosocial support services were identified. Prominent psychosocial issues identified included psychological distress in the form of ‘overthinking’ and ethnic tensions (Adaku *et al*. 2016).

The study will be conducted with the implementing partner, Peter C. Alderman Foundation (PCAF). PCAF is a non-governmental organisation that has collaborated with the Ministry of Health in Uganda to provide mental health support to conflict-affected populations since 2006 (Nakimuli-Mpungu *et al*. 2013). PCAF has a static clinic at the Arua Regional Referral Hospital, a multi-disciplinary team that visits health centres in Rhino Camp on a weekly basis (psychiatric clinical officer, nurse, counsellor, social worker) and a social worker based in the settlement. At the time of this study, all mental health services in the settlement are provided by PCAF and supervised by a psychiatrist [name] based in Arua.

## Current study

Our research strategy is informed by the UK Medical Research Council Framework for the Development of Complex Interventions (Craig *et al*. 2008), which recommends an iterative process of: (a) intervention development, (b) feasibility testing and piloting, (c) evaluation and (d) implementation. This framework for the development of interventions emphasises the importance of exploratory and randomised pilot studies prior to large-scale trials, to address uncertainties such as problems of acceptability, compliance, feasibility, delivery of the intervention, recruitment and retention.

In line with this framework, we conducted two preliminary studies: (1) an uncontrolled pilot of SH+ with one group of men and one group of women (Tol *et al*. 2018*a*); and (2) a feasibility cluster-randomised controlled trial (cRCT) with one group of women in the intervention condition, and one group of women in the control condition (Tol *et al*. 2018*b*). Given the concerns of contamination in small communities and with the provision of an illustrated book, a cluster design was chosen. The initial uncontrolled pilot found good adherence among women, promising changes on outcome measures, and encouraging statements of improvement in qualitative interviews. However, adherence among men was suboptimal and a few sessions were disrupted due to some participants attending while intoxicated. We therefore decided that further adaptation was required for use of SH+ with men, and to continue our evaluation of SH+ with women only. Additional details on the translation, adaptation and initial uncontrolled piloting can be found in this volume (Tol *et al*. 2018*a*).

## Methods

### Design

This study is a two-arm, single-blind, superiority cRCT, to evaluate the effectiveness of the locally adapted SH+ alongside enhanced usual care (EUC) (SH+), compared with EUC alone. It is conducted in a community-based setting with South Sudanese refugee women living in northern Uganda. All villages in the zones of Rhino Camp where preliminary studies of SH+ have not been implemented (*n* = 14) will be included and randomisation will occur at the village level such that half of the villages will be allocated to receive SH+ and EUC and half will receive EUC alone. Outcomes on a range of mental health indicators will be assessed at the individual level at baseline (T1), post-intervention (T2; 6 weeks) and 3-month follow-up (T3; 19 weeks). The Standard Protocol Items: Recommendations for Interventional Trials (SPIRIT) is outlined in Fig. 1, and the checklist is attached as an online Supplementary file.

**Fig. 1. fig01:**
[figure not shown]
Standard Protocol Items Recommendations for Interventional Trials (SPIRIT): schedule of enrolment, interventions and assessments for cRCT of SH+.

### Aims and hypotheses

The primary aim of this cRCT is to assess the effectiveness of SH+ on symptoms of psychosocial distress at 3 months. The secondary aim is to assess SH+ effectiveness using other measures of mental health and wellbeing from pre- to post-intervention, and at a 3-month follow-up. Additional aims are to assess: (1) whether psychological flexibility acts as a mediator of changes on other outcomes; (2) whether treatment effects are moderated by past experience of sexual and other forms of GBV, the number of different types of potentially traumatic events experienced and attendance at sessions. Health service use will be measured as an index of costs to enable preliminary cost-effectiveness analysis. We will assess fidelity to the intervention manual and contamination of the control group by exposure to SH+ materials or content.

We expect that women in the SH+ arm will show significantly greater improvements on all outcome measures both at immediate follow-up and 3-month follow-up compared with the EUC arm. In addition, we hypothesise that psychological flexibility will act as a mediator such that the intervention will lead to improvements in psychological flexibility, which in turn are associated with improvements on outcome measures.

Although the study is not powered to conclusively determine the moderation effects, we will conduct exploratory analyses of potential moderators. We expect smaller but still significant treatment effects for women exposed to GBV and higher levels of exposure to other potentially traumatic events. We also expect that treatment effects will be moderated by attendance such that greater attendance is related to larger effects.

### Sample size

Recent meta-analyses of self-help acceptance and mindfulness-based therapies (Cavanagh *et al*. 2014) and psychoeducational depression courses (Cuijpers *et al*. 2009) have found small-to-medium effect sizes for depression symptoms. Although our primary outcome measure is psychological distress, this literature was used as the best estimate of expected effect size. Utilizing the PowerUp! Tool (Dong & Maynard, 2013), a minimum detectable effect size was calculated using an average cluster size of 42 individuals, 14 clusters, intracluster correlation of 0.012, 20% attrition, 80% power, an *α* level of 0.05 and a two-tailed test. With these specifications, the minimum detectable effect size is 0.219 with a total *N* of 588 (294 per condition). In the completed small feasibility cRCT in this population, <20% attrition was observed (Tol *et al*. 2018*a*).

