### Participants, screening and randomisation

Participants will include any female adult refugee (aged over 18 years) from South Sudan living within study villages in Rhino Camp who: (1) is experiencing psychological distress based on attaining a score of 5 or more on the Kessler 6 (K6; Kessler *et al*. 2010); (2) can understand spoken Juba Arabic (according to self-report). Exclusion criteria will be determined through a structured screening questionnaire administered by trained research assistants, and will include: (1) imminent risk of suicide or other life-threatening risk; (2) observable signs of a severe mental disorder (e.g. psychosis); (3) inability to understand the basic intervention materials (with items 2 and 3 assessed using an observation checklist).

Within each village, households will be randomly selected by spinning a bottle to decide which direction to start in, approaching the first household in that direction and then approaching every fifth house after that. Within households, we will inquire whether there are Juba Arabic-speaking adult women. If more than one woman meets these requirements, we will randomly select one by drawing numbered slips of paper, and screen the woman who drew the slip numbered as one. Potential participants will be screened for eligibility, and recruitment and screening will continue until two SH+ groups (20–25 people per group, or around 40–50 participants in total) have been identified. Assuming that 60% of participants screened will be eligible and willing to participate in the study [conservatively estimated on eligibility rates of 76% in the uncontrolled pilot (Tol *et al*. under 2018*a*)], we estimate needing to screen approximately 1050 individuals. However, screening will be continued until the target sample is achieved. Based on the population statistics ([name], Health Information System Officer, Public Health Section, UNHCR, Geneva) and experiences in preliminary studies (Tol *et al*. 2018*a*, *b*), we estimate that recruiting sufficient participants from each of 14 clusters will be feasible. To ensure participant retention in the study, we aim to keep detailed address information and discuss current location with family members if participants have moved.

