#### Primary outcome: psychological distress

We will measure psychological distress using the K6 (Kessler *et al*. 2010) (*α* = 0.64). This is a brief six-item scale of non-specific psychological distress, screening for the presence of serious mental illness. It has been used in the WHO World Mental Health Surveys and validated in many different countries. Scores range from 0 to 24, and in most applications, a score of 13 or above has been interpreted as indicating a probable serious mental illness (Kessler *et al*. 2003), whereas a score of 5 or more is indicative of moderate or severe psychological distress (Prochaska *et al*. 2012). We will use the K6 as both a screener and an outcome measure.

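### The stated minimum detectable effect of 0.219 does not follow from the inputs listed for it: those inputs give about 0.33 SD, and 80% power at 0.219 is not supported by them

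*Protocol article*

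**What the plan says.** Villages are the unit of allocation. The Design section says that "randomisation will occur at the village level such that half of the villages will be allocated to receive SH+ and EUC" and the other half enhanced usual care alone, which is seven villages per arm.

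The Sample size section names a power tool for multilevel designs and gives its inputs as "an average cluster size of 42 individuals, 14 clusters, intracluster correlation of 0.012, 20% attrition, 80% power", with a two-tailed test at 0.05. It continues: "With these specifications, the minimum detectable effect size is 0.219", for a total of 588 women, 294 per arm. Since 14 × 42 = 588, the total is the number recruited, before attrition. The section mentions no covariate, R-squared or baseline adjustment.

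The primary outcome is a K6 score. The Statistics section tests the hypotheses with a latent growth curve model fitted to all three assessments, including baseline.

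**The concern.** The sentence presents 0.219 as the result of the inputs just listed, so a reader can check it, and the check fails by a wide margin. The gap cannot be put down to detail left to a fuller document. The list looks complete, and the text says that the figure follows from it.

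The figure matters because it tells readers how small an effect the trial could reliably detect. If the result is null or borderline, a quoted 0.219 invites the reading that an effect of about 0.22 SD would probably have been found. The inputs as printed do not support that.

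**Working it through.** **Inputs** (all from the Sample size section)
- Villages J = 14, allocated 1:1, so P = 0.5 and P(1−P)J = 0.25 × 14 = 3.5.
- Recruited per village: 42. Analysed after 20% attrition: n = 0.8 × 42 = 33.6.
- Intracluster correlation ρ = 0.012.
- Power 80%, two-sided 5%.
- Covariates: none listed, so R² = 0.

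**Formula** (two-level cluster-randomised design, standardised outcome)

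SE = √[ ρ(1−R²)/(P(1−P)J) + (1−ρ)(1−R²)/(P(1−P)Jn) ]

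MDES = (t₀.₉₇₅ + t₀.₈₀) × SE, on J − 2 − g df, where g is the number of village-level covariates. Power comes from the noncentral t distribution.

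**Step 1. The listed inputs, with attrition**
- SE = √(0.012/3.5 + 0.988/(3.5 × 33.6)) = √(0.003429 + 0.008401) = 0.1088.
- Multiplier on 12 df: 2.179 + 0.873 = 3.051.
- MDES = 3.051 × 0.1088 = 0.332. With normal quantiles (2.80) it is 0.305.
- Ratio to the stated figure: 0.332/0.219 = 1.52, about 52% larger.
- Power at 0.219: noncentrality 0.219/0.1088 = 2.01, giving 45.7%. A simulation of village means gave 45.9%.

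**Step 2. Can a looser reading without covariates give 0.219?**

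| Reading (two-sided, no covariate) | MDES |
|---|---|
| Attrition applied, t on 12 df | 0.332 |
| Attrition applied, z | 0.305 |
| Attrition ignored, t on 12 df | 0.307 |
| Attrition ignored, z | 0.282 |
| 588 women individually randomised, no clustering, no attrition, z: 2.80 × √(4/588) | 0.231 |

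The last row removes every penalty that the section lists and is still above 0.219. Rounding, or t against z, cannot close the gap.

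**Step 3. What does give 0.219?** Two variants were found.
- R² = 0.5 at both levels, one village-level covariate (11 df), n = 42: SE = √(0.001714 + 0.003361) = 0.0712; multiplier 2.201 + 0.876 = 3.077; MDES = 0.2192.
- A one-sided test with ρ = 0 and no attrition gives 0.2190, but this contradicts the listed two-tailed test and the listed ρ.

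The first variant is the more plausible source. It needs an assumption that the section does not list, and it leaves out the attrition that the section does list.

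**Step 4. The first variant with the stated attrition**
- SE = √(0.001714 + 0.004201) = 0.0769; MDES = 3.077 × 0.0769 = 0.237; power at 0.219 is 73.7%.

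**Step 5. Range over R²** (same at both levels, 11 df, n = 33.6; R² is an assumption, as the document gives none)

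| R² | MDES | Power at 0.219 |
|---|---|---|
| 0 | 0.335 | 45% |
| 0.3 | 0.280 | 59% |
| 0.5 | 0.237 | 74% |
| 0.6 | 0.212 | 83% |

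With attrition applied, R² has to be about 0.57 at both levels before 0.219 is reached.

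**The case against.** The strongest reply is that 46% does not describe the planned analysis. It applies to a comparison of follow-up scores that makes no use of baseline. The growth model in the Statistics section includes baseline K6, so some gain in precision is built in. If 0.219 came from R² = 0.5, the error is an unreported setting plus omitted attrition, and the shortfall is 0.237 against 0.219, about 8% and not 52%. The article is also condensed, and the full protocol may state the R². This stands as a limit on the claim: 0.33 and 46% belong to the listed inputs only. It does not rescue the sentence, which attributes 0.219 to those inputs. Even the most favourable plausible reconstruction misses 80% power once the listed attrition is applied.

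A second reply is that the effect expected from the cited literature is described as small to medium, and that 0.219 is never called the expected effect. With the listed inputs, power is about 84% at 0.35 and 92% at 0.40. This also stands.

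A reader might try to go further and cap R² from the K6 internal consistency of 0.64. That is not sound. The coefficient concerns individual scores, does not carry over to village means, and says nothing about other covariates. Nor is the absence of a source for the intracluster correlation a fault in a condensed article.

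**Conclusion.** The stated figure is wrong as written. Under the listed inputs, without covariates, the minimum detectable effect is about 0.33 SD and power at 0.219 is about 46%. No two-sided calculation without covariates, on 588 women or fewer in 14 villages, gives 0.219.

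The conclusion rests on the standard two-level formula with equal village sizes, 1:1 allocation and attrition spread evenly over villages. The account of where 0.219 came from (R² of 0.5 at both levels, 11 df, no attrition) is an inference from a close numerical match and is not documented.

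A reader might infer that 0.33 is the trial's true sensitivity, that it has only even odds of detecting 0.219, or that it is underpowered for its expected effect. The document supports none of these. The planned model uses baseline data, so actual power at 0.219 may lie above 46% by an amount that depends on an unstated R², and 0.33 still falls within the small-to-medium range that the section cites. The supported conclusion is narrower: 80% power at 0.219 does not follow from what is listed.

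**What to change.** Keep N at 588 and correct the sentence in one of two ways.

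- If no covariate was assumed: state that with 14 villages, 42 women recruited and 33.6 analysed per village, an intracluster correlation of 0.012, 80% power, a two-sided 5% test and t on 12 df, the minimum detectable effect is 0.33 SD.
- If a covariate was assumed: state the covariates and the R² at each level, and apply the 20% attrition. If R² is 0.5 at both levels with one village-level covariate, the figure is 0.24 SD on 11 df.

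The cost is a change of wording and a less favourable published figure, with no extra participants and no change to design or analysis. The Trial status section reports that 3-month data collection is in progress, and the Statistics section says that the analysis plan will be signed before unmasking. The correction can be made in that plan and carried into the results paper.
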